# **2. Objectives**

**Primary Objectives and Outcome Measures**

This study will be carried out in a group of adults (≥21 years old) cigarette smokers (n=1000) from rural Appalachian regions of the United States according to the following aims.

**Aim 1:** Evaluate short-term changes in cigarette smoking patterns, including switching, abstinence from cigarettes, and frequency of smoking between ONPs and NRT. At the conclusion of the Switch Phase, the highest rates of (H1a) complete switching (cigarette abstinence + study product use) and (H1b) abstinence from cigarettes will occur in the ONP group. H1c: ONP participants will smoke the fewest cigarettes per day.

**Aim 2:** Compare product appeal, craving, withdrawal relief, and perceived cigarette dependence between ONPs and NRT. Participants randomized to ONPs will report (H2a) greater product appeal and (H2b) greater reduction in craving and withdrawal symptoms than participants randomized to NRT. H2c: Among complete switchers, ONP participants will report greater reductions in cigarette dependence than NRT participants.

**Aim 3:** Examine sustained changes in tobacco use behaviors, including abstinence from cigarettes, purchase of ONPs/NRT, and continued use of ONPs/NRT. During the Observation Phase, ONP participants will (H3a) have higher rates of abstinence from cigarettes, (H3b) use their study product for a greater number of days, and (H3c) be more likely to purchase their study product than participants in the NRT group. With stubbornly high rates of smoking—and consequently lung and oral cancers—existing approaches have been inadequate and cannot be the sole means to reduce smoking in rural Appalachia. We propose to evaluate the effectiveness of a potentially reduced harm tobacco product, ONPs, which has significant appeal to rural Appalachian smokers. With expertise conducting remote, large-scale switching trials, our team is uniquely suited to conduct this investigation. This urgently needed and innovative study will be critical for public health officials, regulators, and healthcare providers working to reduce cancer disparities in rural Appalachia.

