## Switch Phase

The Switch Phase will start on a participant’s “switch date” and will last for 12 weeks. Study participants will receive a reminder text the day before and on the day of their Switch Day ***(SD Reminder Text).*** The goal of the Switch Phase is to identify whether there are differences in cigarette smoking patterns (i.e., switching to the study product, abstinence from cigarettes, and frequency of smoking) between the ONP and NRT groups. We will also assess potential differences in subjective measures of product appeal, craving and withdrawal relief, and changes in perceived cigarette dependence between groups.

Switch Phase: Product Sample Survey

The Switch Phase product sample survey will be automatically sent via REDCap 4 weeks after switch day. ***(Product Sample Survey).*** Participants will be asked to complete questions on their study product preferences for nicotine concentration and flavor for their next (and last) product shipment. Study staff will call, email or text (any combination based on participant preferences) participants up to 10 times to remind them to complete the survey if they have not completed it within two weeks. ***(Survey Reminder)***

Switch Phase: Mid-Switch Survey

The Mid-Switch Survey will be self-administered via REDCap 6 weeks after the switch date to assess product appeal, craving and withdrawal, perceived cigarette dependence, and smoking and study product use behaviors; this survey will also include an iCO assessment. ***(Survey Message, Mid-Switch Survey)*** Study staff will call, email or text (any combination based on participant preferences) participants up to 10 times to remind them to complete the survey if they have not completed it within two weeks. ***(Survey reminder).***

Switch Phase: Mid-Switch Phone Call

The Switch Phase Mid-Switch Phone Call will occur approximately 6 weeks after the switch date, after participants have received their product shipment. This call will provide an opportunity to check-in with participants to confirm receipt of their final shipment and answer any product- or study-related questions. Participants will also be reminded about completing the Switch Phase assessment survey that occurs at the end of Switch Phase (12-weeks after switch date). ***(Mid-Switch Phone Call Script)*** If study staff are unable to connect with the participant, the participant will be emailed or texted the information ***(Mid-Switch Email).***

Switch Phase: Post-Switch Survey

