## Randomization, Blinding, and Unblinding

All randomization procedures will be stratified to ensure balance within groups. After baseline, participants will be randomized within the secure database, REDCap. Randomization will occur using a stratified block-randomization procedure with small, random sized-blocks. Randomization will be stratified by self-reported cigarette dependence, sex, and ONP use history (ever vs. never). Randomization will be counterbalanced and will not be changed once it is complete.

Participants are not blinded to their study product(s) and are instead active participants in trialing their products.

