**Data Analysis Techniques**

Power Analysis: Biochemically verified 7-day point prevalence abstinence from cigarettes at the end of the 12- week Switch Phase by study arm (ONP, NRT) is the primary outcome of the study and was chosen because it is a critical outcome to inform public health interventions and potential FDA regulations of ONPs. It is also stringent statistically, requiring a sample size that will provide sufficient statistical power to examine the other study outcomes. Although we will not biochemically confirm use of NRT or ONP, biochemical verification of abstinence from cigarettes combined with self-reported use of NRT or ONP is indicative of complete switching. To derive our NRT arm abstinence estimate of 13% we used our prior trial that investigated the effects of NRT sampling on cessation outcomes.^70^ Crucially, this trial included a sample of rural participants; in this rural subsample, the cessation rate was 13%.^70^ We derived our ONP arm estimate of 23% based on our preliminary data. As the goal of that study was not switching, we believe this estimate to be conservative. Assuming 80% retention at the end of the 12-week Switch Phase, a total sample of 800 participants (400 per arm), will provide greater than 95% power to detect a difference in smoking abstinence between the NRT and ONP arms for a two-sided, α=0.05 level chi-squared test. Further assuming 70% retention at the end of the 14-week Observation Phase, a sample of 700 (350 per arm) will provide over 90% power to detect a significant difference between the ONP and NRT arms.

Data Analytic Plan: Statistical analyses will be performed using SAS 9.4. P-values less than 0.05 will be considered statistically significant. Baseline demographics and smoker characteristics will be summarized by arm (ONP and NRT), as appropriate. Continuous variables will be presented as mean ± standard deviation and compared between the arms with t-tests. Categorical variables will be presented as frequencies and proportions and compared with chi-squared tests. Balance of all covariates according to randomization will be confirmed prior to conducting the below analyses. Any imbalanced covariates will be controlled for in regression models.

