Aim 1: The examination of differential levels of (H1a) switching, (H1b) abstinence from cigarettes, and (H1c) cigarettes smoked per day, between the ONP and NRT study arms at the end of the 12-week Switch Phase will be the focus of Aim 1. Hypotheses 1a-b: Complete switching rates and abstinence from cigarettes will be compared between arms using logistic regression analysis, adjusting for baseline variables as needed. In an exploratory analysis, we will also evaluate whether sex modifies the associations between study group and the switching and abstinence outcomes using product interaction terms (see Section C.11). Hypothesis 1c: If needed, we will apply a normalizing transformation to the number of cigarettes smoked per day (e.g., taking the logarithm) before proceeding with the analysis as a means of removing the effects of potential outliers. We will compare cigarettes smoked per day between the two arms using linear regression analysis. The model will adjust for cigarettes smoked per day at baseline and other baseline variables if they are imbalanced.

Aim 2: The focus of Aim 2 is the examination of (H2a) product appeal and (H2b) cigarette craving and nicotine withdrawal at the end of the Switch Phase and (H2c) among complete switchers, change in cigarette dependence from baseline to the end of the Switch Phase between the study arms. Hypothesis 2a: We will examine differences in product appeal between the ONP and NRT arms at the end of the Switch Phase with linear regression models. These models will be adjusted for potential confounders including baseline variables such as age, gender, number of cigarettes smoked per day, and/or randomization stratification factors as necessary; normalizing transformations will be employed if needed. Hypothesis 2b: Similar to hypothesis 1a, the analysis of cigarette craving and withdrawal symptoms will be evaluated with linear regression models adjusting for appropriate confounders. Hypothesis 2c: Among participants who completely switched to their assigned study product, change in nicotine dependence from baseline will be compared between smoking abstainers in the ONP and NRT arms using linear regression analysis, adjusting for baseline nicotine dependence and other variables as outlined in Hypothesis 2a.

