Aim 3: Aim 3 will examine differences between the ONP and NRT arms in (H3a) abstinence from cigarettes, (H3b) number of days the study products are used, and (H3c) purchase and continued use of the study products during the 14-week Observation Phase. Hypothesis 3a: The analysis of abstinence from cigarettes at the end of the Observation Phase will mirror that of hypothesis 1b and will be evaluated with a logistic regression model. Hypothesis 3b: Linear regression analysis will be used to compare the number of days the products are used during the Observation Phase between the ONP and NRT arms; a normalizing transformation will be employed if needed and appropriate baseline characteristics will be adjusted for. Hypothesis 3c: The continued purchase and use of either ONP or NRT after during the 14-week Observation Phase will be compared between the arms with logistic regression analysis, adjusting for all appropriate confounders. Missing Data: In the event of missing data, we will contact participants immediately. If a participant drops out, we will attempt to gather follow-up information by calling and trying to reach the participant through other provided contact information. However, if a participant refuses to be contacted or loses contact with the investigators, we will censor data at point of loss. Two statistical approaches will be used to handle missing data. First, we will use inverse probability weighting with propensity scores. This is a two-step procedure in which we first model the probability of missingness as a function of baseline covariates and previous outcomes. Next, the inverse of the resulting predicted probabilities (from the logistic regression model) will serve as weights in our proposed model of the response. We will compare these results to a more conservative intent-to-treat approach as a final step.

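### The missingness model behind the weights lists baseline covariates and previous outcomes but not study arm, so the weighted comparison is biased if prior smoking predicts dropout differently in the two open-label arms

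*Protocol*

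**What the plan says.** The Missing Data text at the end of section 15 (Data Analysis Techniques) gives two approaches. The first is inverse probability weighting: "we first model the probability of missingness as a function of baseline covariates and previous outcomes", and then "the inverse of the resulting predicted probabilities (from the logistic regression model) will serve as weights in our proposed model of the response". The second is a comparison: "We will compare these results to a more conservative intent-to-treat approach as a final step". No rule for handling missing outcomes is attached to the second.

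The response model for the primary outcome is stated under Aim 1: "Complete switching rates and abstinence from cigarettes will be compared between arms using logistic regression analysis, adjusting for baseline variables as needed". The same section treats covariates as things compared between arms: "Balance of all covariates according to randomization will be confirmed prior to conducting the below analyses". Arm is therefore not naturally one of the baseline covariates.

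On blinding, section 3 says: "Participants are not blinded to their study product(s) and are instead active participants in trialing their products". Aim 2 in section 2 expects the arms to differ in how well the product is liked: "Participants randomized to ONPs will report (H2a) greater product appeal".

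The power analysis assumes abstinence of 13% (NRT) and 23% (ONP), with 80% retention at the end of the Switch Phase and 70% at the end of the Observation Phase. Retention is not given by arm.

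**The concern.** Inverse probability weighting recovers the comparison among everyone randomised only if the observation model conditions on whatever drives both response and outcome. Here one model is described, with two groups of predictors, neither of which is arm. Participants with the same baseline profile and the same earlier smoking status then get the same weight in both arms.

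That is harmless if earlier smoking status predicts dropout in the same way in both arms. It is not harmless if, say, people still smoking leave the NRT arm more readily than abstainers do, while in the ONP arm smokers and abstainers leave equally. The pooled probability is then wrong for both arms, in opposite directions. Participants know their product, and the protocol itself expects differences in appeal, craving and smoking, so a difference in who stays is plausible. With 20% to 30% planned loss there is room for it to matter. At stake is the 10-point abstinence difference on which the trial is powered.

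**Working it through.** **The plan's own figure.** For 13% vs 23%, two-sided α = 0.05, pooled variance under the null, with mean rate 0.18:

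power = Φ{[0.10 − 1.96·√(2·0.18·0.82/n)] / √[(0.13·0.87 + 0.23·0.77)/n]}

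- n = 400 per arm: (0.10 − 0.0532)/0.0269 = 1.74, power 95.9% (stated: above 95%).
- n = 350 per arm: (0.10 − 0.0569)/0.0288 = 1.50, power 93.3% (stated: above 90%).

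The stated power reproduces and is not in question.

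**Inputs for the weighting check.** From the protocol: 13% and 23%, equal arms, about 80% retention at week 12. Assumed, because the documents do not give them: week-6 abstinence of 18% (NRT) and 30% (ONP); 4% of week-6 smokers abstinent at week 12; and the loss by arm and week-6 status shown in the table. Week-12 abstinence among week-6 abstainers then follows:

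- NRT: (0.13 − 0.82·0.04)/0.18 = 0.540
- ONP: (0.23 − 0.70·0.04)/0.30 = 0.673

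**Formula.** Let f be the share of an arm with week-6 status s, r the probability of being observed, and y the week-12 abstinence rate. The pooled model gives π(s) = Σ f·r / Σ f, summed over the arms. Each cell gets weighted mass W = f·r/π(s), and the weighted rate in an arm is ΣW·y/ΣW. The weight is taken as 1/P(observed). The protocol's wording about which probability is inverted is a separate matter.

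**One case in full: dependence in NRT only** (NRT smokers lose 23%, NRT abstainers 5%, all ONP 20%).

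- π(smoker) = (0.82·0.77 + 0.70·0.80)/1.52 = 0.784
- π(abstainer) = (0.18·0.95 + 0.30·0.80)/0.48 = 0.856
- NRT: masses 0.6314/0.784 = 0.806 and 0.171/0.856 = 0.200; abstainer share 19.9% instead of 18%; weighted rate 13.9%
- ONP: masses 0.560/0.784 = 0.714 and 0.240/0.856 = 0.280; abstainer share 28.2% instead of 30%; weighted rate 21.8%
- Weighted difference 7.9 points (from unrounded rates)

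**All patterns** (true difference 10.0 points; loss given as smokers/abstainers at week 6):

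| NRT loss | ONP loss | Retention NRT/ONP | Unweighted completers | Weights without arm |
|---|---|---|---|---|
| 23%/8% | 23%/8% | 79.7%/81.5% | 11.1 | 10.0 |
| 23%/8% | 24%/12% | 79.7%/79.6% | 10.6 | 9.7 |
| 22%/12% | 24%/10% | 79.8%/80.2% | 11.4 | 10.5 |
| 23%/8% | 22%/14% | 79.7%/80.4% | 9.9 | 9.2 |
| 23%/5% | 20%/20% | 80.2%/80.0% | 8.3 | 7.9 |
| 20%/20% | 26%/5% | 80.0%/80.3% | 13.5 | 12.4 |

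Fitting by arm makes π equal r in every cell, so W = f and the difference is 10.0 points in every row. Retention is nearly equal between arms in most rows, so comparing retention rates would not reveal the problem. With no true effect (13% and 18% week-6 abstinence in both arms), the last two patterns give −1.6 and +1.8 points.

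**Is a main effect of arm enough?** A second calculation used a binary baseline covariate (50% prevalence, log-odds −0.8 on abstinence), week-6 status (log-odds 3.0 on week-12 abstinence) and true rates of 13% and 23%.

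- Predictors act in NRT only, 80%/80% retention: 8.2 points without arm, 8.1 with an arm main effect, 10.0 with arm interactions.
- Predictors act alike, retention 75%/85%: 9.1 without arm, 10.0 with a main effect.
- Dropout depends on arm alone, 75%/85%: 9.9 without arm.

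**The case against.** The strongest reply is that the sentence is a summary. It does not say that only these predictors are used, or that arm is excluded, and the exact terms of a weight model often sit in the SAP, which is not at hand. That limits how firmly one can call this an error. It does not remove the point: the protocol names its predictors, arm is not among them, and no other section adds it. An analyst who followed the text would fit the pooled model.

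The second reply is about size, and it largely stands. The 7.9 and 12.4 figures assume strong dependence on smoking in one arm and none in the other. Milder differences shift the result by less than a point, and a shared pattern gives no bias. The open-label design and the expected differences in appeal make differential dropout plausible. They do not show that smoking status predicts it differently by arm. Nor is weighting always worse than ignoring the loss: it is in the NRT-only case (7.9 vs 8.3), but it helps in the ONP-only case (12.4 vs 13.5).

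A reader might also infer that anyone who missed the week-6 survey would be deleted from the weight model and lose an observed week-12 outcome. The protocol does not support that. It does not describe a single unstaged model or listwise deletion, and its term for earlier outcomes is general. Week 6 is also not the first measurement after randomisation: section 3 has an iCO reading at the pre-sampling call, and a survey with iCO at the end of the Sampling Phase.

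**Conclusion.** The point holds in a conditional form. As listed, the predictors of missingness omit arm, and weights built that way leave the comparison biased if earlier smoking status predicts dropout differently in the two arms. Against a true 10.0 points, the weighted difference ranges from 10.0 (same pattern) through 9.2 to 10.5 (mild differences) to 7.9 or 12.4 (dependence in one arm only). The direction cannot be known in advance.

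These figures rest on assumed week-6 abstinence and dropout, because the documents give no retention by arm or by smoking status. They show what could happen and do not predict what will. It would be too strong to say that the weighted result will be biased, or that it is valid only if dropout is identical in both arms: when dropout depends on arm alone, the distortion is about 0.1 point. The comparison with the intent-to-treat approach does not settle the matter, since no rule for missing outcomes is given for it. The power statement is unaffected.

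**What to change.** Add a sentence to the Missing Data text: the model for the probability of being observed is fitted separately in each arm, or includes arm and its interactions with previous outcomes and key baseline covariates. A main effect of arm alone should not be taken as sufficient. Building the model visit by visit is optional good practice and not needed to meet this point.

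No new data are required. The cost is somewhat more variable weights, because more terms are estimated. The change should be made before dropout by arm is seen, so that the choice is not open to the charge of being made after the fact.

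### The missing-data weights are inverted as written: the plan weights by the inverse of the probability of being missing, not of being observed

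*Protocol*

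**What the plan says.** Protocol section 15, Data Analysis Techniques, names two approaches to missing data. The first is introduced with "First, we will use inverse probability weighting with propensity scores" and set out in two steps. Step one: "we first model the probability of missingness as a function of baseline covariates and previous outcomes". Step two: "the inverse of the resulting predicted probabilities (from the logistic regression model) will serve as weights in our proposed model of the response". The second approach is a comparison: "We will compare these results to a more conservative intent-to-treat approach as a final step". The protocol does not define that comparison further, and nothing elsewhere in it takes the complement of the modelled probability or redefines the modelled event as being observed.

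The Power Analysis text in the same section plans for 80% retention at the end of the Switch Phase (800 of 1,000, 400 per arm) and 70% at the end of the Observation Phase (700, 350 per arm). So about 20% of outcomes are expected to be missing at the primary time point and about 30% at the later one. Assumed abstinence is 13% with NRT and 23% with ONP.

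**The concern.** Inverse probability weighting lets the observed participants stand in for similar people who were lost. Someone with a profile prone to dropout, but who stayed, must count for more than one person. That requires a weight of 1/P(observed). The only probability that the plan's first step produces is P(missing), and the second step inverts it directly. The resulting weight is largest for people who were almost certain to stay and smallest for those who resemble the dropouts, which is the reverse of the method's purpose.

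This is not detail left open for a statistical analysis plan. The protocol states the rule, and the two sentences agree with each other. A programmer who followed them would build the wrong weight in the first-listed missing-data analysis.

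**Working it through.** **Inputs from the protocol (section 15):** abstinence 13% and 23%; retention 80% and 70%; 400 and 350 per arm analysed; two-sided alpha 0.05, chi-squared test.

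**Inputs assumed here for illustration:** how missingness and abstinence vary with a baseline characteristic. The protocol gives no such figures.

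**1. The plan's own power figure.** Power = Phi{[|p1 - p2| - 1.96 x sqrt(2 x pbar x (1 - pbar)/n)] / sqrt([p1(1 - p1) + p2(1 - p2)]/n)}, with pbar = 0.18.
- n = 400: (0.10 - 0.0532)/0.0269 = 1.74, power 95.9%.
- n = 350: (0.10 - 0.0569)/0.0288 = 1.50, power 93.3%.

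The stated figures (above 95% and above 90%) reproduce. They describe an unweighted test and are not affected by this point.

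**2. Exact two-stratum check.** Two equal strata have missingness of 10% and 30% (mean 20%) in both arms. Abstinence is 19% and 7% with NRT (mean 13%), and 33% and 13% with ONP (mean 23%). The weighted mass of a stratum is 0.5 x P(observed) x weight.

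| Weight | Low-dropout stratum | High-dropout stratum | High-dropout share |
|---|---|---|---|
| 1/P(observed) | 0.45 x 1.11 = 0.50 | 0.35 x 1.43 = 0.50 | 50% |
| none | 0.45 | 0.35 | 43.75% |
| 1/P(missing), as written | 0.45 x 10 = 4.50 | 0.35 x 3.33 = 1.167 | 1.167/5.667 = 20.6% |

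Estimated abstinence follows from those masses:
- Correct weights: NRT 13.0%, ONP 23.0%, difference 10.0 points (the truth).
- No weighting: 13.75% and 24.25%, difference 10.5.
- As written: NRT (4.50 x 0.19 + 1.167 x 0.07)/5.667 = 16.5%; ONP (4.50 x 0.33 + 1.167 x 0.13)/5.667 = 28.9%; difference 12.4.

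**3. One large simulated arm.** It has 400,000 people, 20% missing, a fitted logistic missingness model, a missingness slope of 0.8 and an abstinence slope of -0.8 per SD of one baseline covariate. True abstinence was 22.93%. Correct weights gave 22.96%, no weighting 24.6% and the literal weights 34.4%. The effective sample size was 97% of those observed with correct weights and 61% with the literal ones.

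**4. Simulated trials.** These had 500 per arm, a true 13% vs 23%, 20% missing by the same mechanism in both arms, and an outcome model without the covariate.

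| Analysis | Mean difference | Empirical SE | Power |
|---|---|---|---|
| Correct weights | about 9.8 | 2.6 | 97% |
| Observed participants, unweighted | 10.4 | not tabulated | not tabulated |
| Literal weights | about 13.0 | about 4.4 | 85% |

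**5. Study arm in the missingness model.** There was no true effect (18% in each arm), with dropout of 25% on NRT and 15% on ONP and assumed missingness slopes of 1.0 and 0.5. Correctly inverted weights from a model with arm and arm-by-covariate terms gave 0.0 points of bias and 5.5% type I error. Correctly inverted weights without arm left -1.6 points and 11%.

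**The case against.** **It may be a slip of wording.** The plan names a standard method, and the error amounts to writing missingness where being observed was meant. An analysis plan could state the right weight, and a second analysis is planned for comparison. This is a fair reading of intent. It does not change what the two sentences say, and the comparison analysis does not define or correct the weights.

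**Covariate adjustment limits the bias.** Section 15 plans logistic regression adjusted for baseline variables as needed. If the covariate driving dropout is in the outcome model, weights built from it do not bias the conditional arm effect. In simulation the arm log-odds ratio was 0.748 with the literal weights and 0.745 with correct ones. What remained was lost precision, with power of about 88% against 98%. This stands, although bias could still enter through previous outcomes or covariates left out of the model.

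**Stronger readings that the protocol does not support:**
- A reader might infer gross type I error. With unequal dropout and no true effect, the literal weights can give about 34% type I error, and power can fall to about 31% when the effect is real. Both need arm-by-covariate terms in the missingness model, which the protocol does not list, and slopes that differ by arm. With baseline covariates only, the same settings gave -1.2 points and 5.8% type I error under no effect, and 12.2 points and 81% power under 13% vs 23%.
- A reader might infer that the literal weights are always worse than an unweighted analysis of observed participants. In that same no-effect setting the unweighted analysis was slightly more biased, at -1.4 points with 8.5% type I error.
- A reader might take the intent-to-treat comparison to count missing as smoking and criticise it on that basis. The protocol states no such rule.
- Robust standard errors, the exact model terms and the choice of primary analysis commonly belong in the statistical analysis plan, so their absence here is not an error.

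**Conclusion.** The point holds as an error in a stated formula. As written the weight is 1/P(missing); it should be 1/P(observed). That conclusion needs no assumption beyond the fact that only observed participants enter the response model.

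Its effect is conditional. In the two-stratum illustration a true 10.0 points becomes 12.4, and the high-dropout stratum's share falls from 50% to 20.6%. With a common dropout mechanism and an unadjusted outcome model, the standard error rises from about 2.6 to 4.4 points and power falls from about 97% to 85%. Other dropout patterns change the size or direction of the bias, and adjusting for the covariate that drives dropout leaves mainly a loss of precision. With 20% to 30% of outcomes expected to be missing, the rule should be corrected before any data are analysed.

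**What to change.** Replace the two sentences that define the weights with: *model the probability that the outcome is observed, given study arm, baseline covariates and previous outcomes, and weight each observed participant by the inverse of that probability.*

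Naming study arm goes beyond correcting the inversion. It guards against dropout that differs between the products and costs nothing. Whether to add arm-by-covariate terms, which the check in step 5 of the working included, can be settled in the statistical analysis plan.

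The cost is one sentence of protocol text. No extra data, visits or participants are needed, and the sample size justification is unchanged.
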